**Methods:**

The initial recruitment was estimated at 112 people with idiopathic PD. Two-thirds of the participants will be randomized to one of the two groups to make the crossover. In contrast, the other third will do a face-to-face group program only. The balanceHOME protocol consists of challenging balance exercises incorporated into functional daily tasks, developed in-home and conducted two times per week for 60-min over an 8-weeks period. The primary strategy will consist of splitting functional tasks of daily life into static and dynamic balance components, besides standardized facilitate and disturbing strategies to execution of each exercise. Biomechanics and clinical performance of balance and gait, perception of quality of life, cognitive and mental functioning, and severity of PD will be measured at baseline (T0), post-8 weeks training (T1), and follow-up (T2).

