#### Outcomes and participant timeline

2.2.3.

First, during the enrolment assessment, a standardized neurological clinical interview for Parkinson’s Disease (Supplementary material 4) will be performed. This interview includes questions related to habits, disease start, education, and working life. At the same time, weight, height, and body mass index will be measured with a wall stadiometer and a TANITA SC-240MA scale. The length of the lower limbs will also be measured during standing position with a tape measure from the anterior superior iliac spine and the medial malleolus. Asymmetries between the lower extremities greater than 1 cm will be considered within the first exclusion criteria (comorbidities that affect balance or gait). As mentioned above, each phase of the study has three evaluation moments: baseline (T0), post-8-week-training (T1), and follow-up (T2) at 8 weeks after the physiotherapy programs have finished. Assessments will be performed by a different physiotherapist from recruitment and treatment besides a neuropsychologist, both blinded to the treatment assignment. The participants will be evaluated in an ON-medication state (1 h after the dopaminergic dose) on the schedule described in Figure 1. In each measurement session, the severity of the disease (Hoehn and Yahr, 1967; Fahn et al., 1987), cognitive and mental status (Hamilton, 1959, 1960; Mahieux et al., 1995; Dubois et al., 2000; Marinus et al., 2003), perception on quality of life (Peto et al., 1995; Powell and Myers, 1995; Sandín et al., 2020), and balance and gait performance will be registered through clinical tests (Tinetti, 1986; Giladi et al., 2000; Kegelmeyer et al., 2007; Franchignoni et al., 2010) as well biomechanics instruments. Table 2 shows the scales and clinical tests that will be used to evaluate the participants. For balance biomechanics, assessment will be used a dynamometric platform (Dinascan/IBV Biomechanics Institute of Valencia, Valencia, Spain) and the NedSVE®/IBV software (version 5.3.0.1, Biomechanics Institute of Valencia, Valencia, Spain). Balance will be assessed through the Romberg tests under four static conditions with increasing difficulty (see Figures 2A,B): (i) eyes open; (ii) eyes closed; (iii) eyes open on a foam rubber; and (iv) eyes closed eyes on the foam rubber (thickness of 9 cm, 56.7 kg/m3 of density, and resistance of 25%) (Escamilla-Martínez et al., 2021). Participants were asked to find the most stable position while barefoot with their arms relaxed on either side of the body, with their heels together and toes apart at a 30° angle. Additionally, four static functional balance tests will be assessed, using the Romberg test protocol with their eyes open: (i) to see the time on an analogy clock (visual); (ii) to answer a simple question (verbal); (iii) to pour the contents of one glass into another (lower motor); and (iv) to simulate comb the hair (upper motor). The instructions for each task were standardized to ensure uniform execution of the gesture. Participants will be asked to remain as still as possible with their heads in a neutral position and their gaze forward, except for the lower motor test where they will be allowed to observe their hands. Each test will last for 30 s and will be recorded two times. Finally, dynamic balance will be assessed with stability limits and rhythmic weight shift tests on the platform (Balaguer García et al., 2012). In the stability limits test, participants from the Romberg position will have to move a cursor (which reflected the position of their CoP) toward eight targets (front, front-right, right, rear-right, rear, rear-left, left, and front left) visualized on a computer monitor placed in front at their eye level. Once the target is reached, the subject will have to maintain the posture with the CoP displaced at the limit of stability until the end of the 8 s of each test (Balaguer García et al., 2012). On the other hand, in the rhythmic weight shifts tests, subjects will have to move their CoP to the direction and velocity of a moving target visualized on the computer monitor (Balaguer García et al., 2012). Each dynamic test will be registered two times. As a result, the primary outcome of the study will be the CoP sway area, which is defined as the surface over which the CoP moves during the measurement and is a valid indicator of detecting postural control changes in dual-task conditions (Campolettano et al., 2020; Morenilla et al., 2020). The secondary outcomes are shown in Table 2 and consist of biomechanics and clinical variables related to static and dynamic balance.

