#### Sample size and recruitment

2.2.4.

The software G*Power v.3.1 (Faul et al., 2007) has been used to determine the necessary sample size to detect a change in the primary outcome CoP sway area and differences between the groups (EG, PCG, ACG), with a small-medium effect (*f* = 0.15), a statistical significance of 5% at the two-tailed level, and a power of 95%. As a result of the above, 93 people diagnosed with PD will be recruited. If 20% of possible dropouts are also considered during the study, the initial recruitment should be 112 people. The sampling process will consist in the consecutive non-probabilistic method, in which the selection of individuals is carried out based on the fulfillment of participation criteria. The recruitment of participants began on 1 July 2021 and we estimate its completion on 31 July 2023. The participant recruitment procedure consists of three steps. First, the neurorehabilitation center has selected the possible candidates for the study based on personal and clinical characteristics, asks them by email the authorization to send information about the study, and contacted them using their telephone number. Then, the principal investigators called potential candidates to resolve possible doubts and confirm their participation. Finally, a physiotherapist will assess the selection criteria for all the volunteers and will provide informed consent for their signatures. The recruitment process will be repeated to complete the number of participants estimated for the study, extending participation to a new clinical center or public hospital if necessary.

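### The 95% power stated for 93 participants holds for the three-assessment group-by-time test only if the unstated correlation is about 0.67 or more; at 0.5 it is about 81%

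*Protocol article*

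**What the plan says.** Section 2.2.4 (Sample size and recruitment) uses "The software G*Power v.3.1" to find the number needed "to detect a change in the primary outcome CoP sway area and differences between the groups (EG, PCG, ACG"), with f = 0.15 and "a statistical significance of 5% at the two-tailed level, and a power of 95" per cent. It then concludes: "As a result of the above, 93 people diagnosed with PD will be recruited". Those are all the inputs it prints. The test procedure, the number of repeated measurements, the correlation between them and the non-sphericity correction are not given.

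The schedule is set elsewhere. Section 2.2.3 says that "each phase of the study has three evaluation moments: baseline (T0), post-8-week-training (T1), and follow-up (T2"). Section 2.1 describes a crossover into a second phase for the experimental group (EG) and the passive control group (PCG) only. For the active control group (ACG), the Abstract says that "the other third will do a face-to-face group program only". Section 2.4 answers the main aim with a mixed analysis that has assessment time as the within-subject factor and group as the between-subject factor.

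**The concern.** The number 93 is presented as following from the printed inputs. For the design that all three groups share, three groups by three assessments, it does not follow at the correlation of 0.5 that is G\*Power's default. It does follow at that correlation if six assessments are entered, and the text gives six only to the two crossover groups. The wording also covers two targets, change and group differences, which have very different power at the same sample size.

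At stake is how a null result is read. A reader who trusts 95% power takes the type II error at the assumed effect to be 5%. At a correlation of 0.5 it would be about 19% for the interaction, and it stays above 5% at any correlation below about 0.67.

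**Working it through.** **Inputs from the document.** f = 0.15, so f² = 0.0225; alpha 0.05; k = 3 groups; N = 93 (section 2.2.4). m = 3 assessments per phase (section 2.2.3). An F test offers no choice of sidedness, so 0.05 is used as it stands.

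**Assumed, because the document gives neither.** Correlation ρ between assessments, varied below, and ε = 1 (sphericity).

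**Formula for the within-between interaction (noncentral F).** λ = N f² m ε / (1 − ρ); df1 = (k − 1)(m − 1)ε; df2 = (N − k)(m − 1)ε.

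**Step 1: reproduce the printed 93.** Take k = 3, m = 6, ρ = 0.5.
- λ = 93 × 0.0225 × 6 / 0.5 = 25.11, with df 10 and 450. Power is 0.952.
- At N = 92, power is 0.9495. So 93 is exactly the smallest N for 95% with six assessments.

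**Step 2: the three shared assessments.** Take k = 3, m = 3, ρ = 0.5.
- λ = 93 × 0.0225 × 3 / 0.5 = 12.555, with df 4 and 180. Power is 0.811.
- 95% needs N = 140, or 141 in three equal groups.
- 80% needs N = 91, which rounds up to 93 in three equal groups.

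**Step 3: vary the unstated correlation** (N = 93, m = 3, ε = 1; λ = 6.2775 / (1 − ρ)).

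| ρ | Interaction power |
|---|---|
| 0.3 | 0.65 |
| 0.4 | 0.73 |
| 0.5 | 0.81 |
| 0.6 | 0.90 |
| 0.67 | 0.95 |
| 0.7 | 0.97 |

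The crossing point for 95% is ρ ≈ 0.671. Departure from sphericity lowers the figures: at ε = 0.75, power is 0.72 at ρ = 0.5 and 0.89 at ρ = 0.67.

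**Step 4: the between-group main effect.** λ = N f² m / (1 + (m − 1)ρ) = 6.2775 / (1 + 2ρ), with df 2 and 90.
- ρ = 0.5: λ = 3.139, power 0.325; 95% would need 462 in equal groups.
- ρ = 0: λ = 6.278, power 0.589. This is the maximum over non-negative ρ, since λ falls as ρ rises.
- ρ = 0.67: λ = 6.2775 / 2.34 = 2.683, power 0.28.

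A higher correlation therefore raises interaction power and lowers main-effect power. No non-negative correlation gives 95% for both at N = 93.

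**The case against.** The strongest defence is that 0.5 is a software default and not a value from the document. With a correlation between about 0.671 and 0.681, the three-by-three design itself returns 93 at 95% power in equal groups, and repeated sway measurements could plausibly correlate that strongly. This stands. It rules out saying flatly that the power is 81% or that the type II error is 19%; both are conditional on 0.5.

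A reader might also infer that six assessments were entered by mistake. The match is exact, but section 2.2.4 never mentions six. Three sets of inputs lead to 93: six assessments at 95% power and ρ = 0.5; three assessments at 80% power and ρ = 0.5; three assessments at 95% power and ρ of about 0.67 to 0.68. The documents cannot say which was used. Figure 1, which carries the schedule, is not shown, although the text describes a single phase for the ACG.

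Third, the crossover adds information. If 62 of the 93 cross over, there are 62 + 62 + 31 = 155 person-phases. But phases from the same person are not independent, the groups become unequal, and section 2.2.4 counts people in three groups. This is a reason to say what the calculation covers. It is not a derivation of 95%.

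Fourth, the target is ambiguous. The within-subject time effect alone has 89% power at ρ = 0.5 and about 95% at ρ = 0.60. That effect does not compare the groups, whereas the sentence claims group differences and the Introduction's hypothesis is comparative.

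Finally, a condensed article may leave software settings to the full protocol. That excuses the omission as such. It does not excuse printing 95% as the consequence of inputs that do not produce it for the described design without an unstated high correlation.

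**Conclusion.** The sentence is wrong as written, in a limited sense: 95% power does not follow from the printed inputs and the T0-T1-T2 schedule unless the correlation is about 0.67 or higher with sphericity, and no such value is stated. At an assumed 0.5, interaction power is about 81%, and over correlations of 0.3 to 0.7 it runs from 65% to 97%. Because that range contains 95%, the documents do not show that the trial is underpowered, nor that 141 people must be enrolled. What can be said without choosing a correlation is that the between-group main effect cannot have 95% power at this size: it has at most 59% at any non-negative correlation, and about 33% at 0.5.

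**What to change.** In section 2.2.4, restate the power for the group-by-time interaction with three groups and three assessments, and name the procedure. Give the correlation with its source, and the epsilon used.

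- If a source supports a correlation of about 0.67 or more, cite it; 95% can then stand for the interaction, provided the epsilon used also gives it.
- If none does, replace 95% with the power at the assumed correlation (about 81% at 0.5 with epsilon 1), and show the range from 65% at 0.3 to 97% at 0.7.
- If six assessments were entered, remove that basis, because the text gives the ACG three.
- Do not claim 95% power for the between-group main effect.

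The cost is a sentence or two in one section and possibly a less favourable power figure. No additional participants are needed.

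### The 20% dropout allowance was added to 93 instead of being taken out of the recruits: 112 protects 93 only up to 17.0% dropout, and the figure consistent with 20% is 117 (minor correction)

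*Protocol article*

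**What the plan says.** Section 2.2.4 (Sample size and recruitment) reports a G*Power calculation for the primary outcome, CoP sway area, in three groups. It uses an effect of f = 0.15 and "a statistical significance of 5% at the two-tailed level, and a power of 95" per cent. The result is given as: "As a result of the above, 93 people diagnosed with PD will be recruited". The dropout step follows directly: "If 20% of possible dropouts are also considered during the study, the initial recruitment should be 112 people".

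The Abstract (Methods) repeats the inflated figure: "The initial recruitment was estimated at 112 people with idiopathic PD". It also gives the split between the arms: "Two-thirds of the participants will be randomized to one of the two groups to make the crossover", with the remaining third in the face-to-face programme.

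The article gives no inflation formula and no second dropout rate. Section 2.2.4 adds that the recruitment steps will be repeated until the estimated number is reached, but it does not say that dropouts will be replaced beyond 112.

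**The concern.** A dropout allowance is meant to ensure that the required number remains after the expected losses. If a fraction d of the recruits is lost, the number to recruit is n / (1 - d). Multiplying n by (1 + d) always gives too few, because the losses then fall on the enlarged group.

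The stated 112 matches the multiplicative form. If so, the headline recruitment target, which appears in two places, does not follow from the dropout rate printed beside it. At that rate the trial would end with fewer participants than the number on which its power statement rests.

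**Working it through.** **Inputs.** Required number 93, dropout 20% and recruitment 112 are all in section 2.2.4, with 112 repeated in the Abstract (Methods).

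**Step 1: reproduce the plan's figure.** n x (1 + d) = 93 x 1.20 = 111.6, rounded up to 112. This matches the stated figure.

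**Step 2: what 112 leaves at 20% dropout.** Losses: 112 x 0.20 = 22.4. Remaining: 112 x 0.80 = 89.6, so 89 rounded down or 90 rounded to nearest. The shortfall against 93 is 3 to 4. Spread evenly over three groups, that is about one participant per group (3.4 / 3 = 1.1).

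**Step 3: the consistent inflation.** n / (1 - d) = 93 / 0.80 = 116.25, rounded up to 117. Check: 117 x 0.80 = 93.6, at least 93; 116 x 0.80 = 92.8, just below. The gap to the stated figure is 117 - 112 = 5 recruits.

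**Step 4: the dropout rate that 112 covers.** (112 - 93) / 112 = 19 / 112 = 0.170, or 17.0%.

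**Step 5: the effect on power.** The article does not state which test was powered, the number of measurements, the correlation between them or a sphericity correction. One setting that returns 93 is a repeated-measures within-between interaction with k = 3 groups, m = 6 measurements, correlation rho = 0.5 and sphericity. Six could be three assessments in each of two phases, since the article says that "each phase of the study has three evaluation moments: baseline (T0), post-8-week-training (T1), and follow-up (T2"), but that is an inference. The noncentral F has

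- noncentrality = f² x N x m / (1 - rho) = 0.0225 x N x 6 / 0.5 = 0.27 x N
- numerator df = (k - 1)(m - 1) = 10
- denominator df = (N - k)(m - 1) = 5 x (N - 3)

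| N | Noncentrality | Denominator df | Power at alpha 0.05 |
|---|---|---|---|
| 93 | 25.11 | 450 | 0.952 |
| 90 | 24.30 | 435 | 0.944 |
| 89 | 24.03 | 430 | 0.941 |

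The loss is 0.952 - 0.944 = 0.008 to 0.952 - 0.941 = 0.011, about 1 point.

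**The case against.** Four points can be made for the plan.

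- **The 20% may be a share of 93.** Adding a fifth to 93 gives exactly 112, and the article prints no formula. This explains how the number arose, but it does not describe dropout during a study. If a fifth of those enrolled leave, 93 do not remain. On this reading the real allowance is 17.0% of recruits, and the text should say so.
- **20% is an allowance, not a forecast.** This stands. If dropout is 17.0% or less, 112 still leaves 93. A reader might infer that 112 can never deliver the required number. The document does not support that: the shortfall arises only above 17.0%, which includes the plan's own 20%.
- **Analysis is by intention to treat (section 2.4), and nothing limits it to completers.** This stands in part, since someone who leaves late may still contribute data. But section 2.2.4 itself treats dropouts as eroding the 93. The mixed MANOVA over assessment times in section 2.4 ordinarily needs complete repeated measures, and the article describes no imputation.
- **Recruitment will be repeated as needed.** Section 2.2.4 ties this to reaching the estimated number, not to replacing losses beyond it.

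None of these removes the mismatch between 93, 20% and 112. They do limit its weight.

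**Conclusion.** The arithmetic error is certain and its effect is small. At 20% dropout, 112 recruits leave about 89 to 90 participants instead of 93; the matching recruitment number is 117. These figures use only numbers printed in the article and the ordinary meaning of a dropout rate as a share of those recruited. They hold whether or not 93 is itself well founded.

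The power loss of about 1 point rests on the assumed setting in the working (6 measurements, correlation 0.5, sphericity). There the design stays at about 94% against a nominal 95%. No test, allocation or conclusion changes, so this is a minor correction.

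A reader might infer that the dropout step leaves the trial seriously underpowered, for instance by entering 3 measurements and correlation 0.5 in the same formula, which asks for 141 instead of 93. The document does not support that inference. It states neither value, and under that setting 93 would not give 95% power even with no dropout. That gap would come almost entirely from the assumed number of measurements, not from the inflation.

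**What to change.** Amend the Abstract (Methods) and section 2.2.4 so that the three figures agree. The least costly way is to keep 112 and state that it allows for 17% dropout, or equivalently that it leaves about 89 to 90 participants at 20%, with a note that 117 would be the number consistent with 93 and 20% dropout. This costs one sentence in section 2.2.4 and a matching phrase in the Abstract, with no extra participants and no change to the design.

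If the sponsor prefers to keep the full 20% allowance, the target becomes 117 in both places, at a cost of 5 more recruits.

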### Assignment of interventions and blinding

2.3.

An external investigator will perform the randomization process (1:1). Stratified randomization will be carried out according to PD severity and general cognitive state and assigned to one of the two groups for crossover, EG or PCG. A matched-pairs design will be created in which participants were allocated to these two groups taking into consideration the outcomes, i.e., Hoehn and Yahr state (I-II-III-IV) and Mini Mental Parkinson Test score (≥ 25, normal cognitive function or ≤ 24, altered cognitive function) at T0. The principal investigators will be responsible for the management of participants’ appointments after being assigned by telephone. On the other hand, the physiotherapist evaluator will be blinded to the assignment of the groups. For this reason, it will be explained to the participants that they do not reveal information about their intervention during the assessment sessions. Due to the nature of interventions, the patients and the physiotherapist who develop the rehabilitation cannot be blind to the treatment to be performed, but the hypothesis of the study will be hidden. Additionally, after the consent signature, participants will be assigned a numeric code to hide the group of intervention.

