### Data collection, management, and statistical analysis

2.4.

Both evaluators (physiotherapist and neuropsychologist) will be responsible for exporting and filling in a database with variables from the scales and tests mentioned in Table 2 according to the code assigned to each patient to ensure his or her anonymity. To protect confidentiality during the study, the personal information of participants will be located separately from the main dataset on a local computer. The raw dataset will be maintained for 10 years after the completion of the trial with indefinite restricted access due to sensitive data. After the publication of the results trial, a fully anonymized patient-level dataset will be made publicly available on the registration trial website (clinicaltrials.gov). For participation in this study, no participant will receive any kind of incentives or compensation.

All analyses will be evaluated by intention-to-treat principles in terms of assignment to treatment and used a level of significance of 0.05. There are no interim analyses planned for this study. We will use the statistical software SPSS Statistics version 24.0 (IBM Corporation) for all the statistical analyses. Categorical variables were presented using frequency and percentage, and continuous variables as mean with standard deviation if they follow a normal distribution. To test for possible carryover effects of the experimental group, the sum of the values measured in the two periods for each subject will be calculated and compared across the two randomized groups (EG and PCG) using a test for independent samples (Serrao et al., 2019). There should be no difference if there is no sequence (balanceHOME program—usual daily activity or usual daily activity—balanceHOME program) effect.

To answer to the main aim of the study, a two-factor mixed multivariate analysis of variance (MANOVA) test was conducted to analyze the effects of within-subject factors (assessment times) and the between-subject factor (group) on the outcomes registered. The Bonferroni adjustment was used for *post-hoc* comparisons, and differences were declared statistically significant if the value of *p* was less than 0.05. Differences between groups for demographic outcomes were verified with a univariate analysis of variance (ANOVA) between-subjects test. Furthermore, to test for sex differences between groups, a chi-square analysis was used (San Martín Valenzuela et al., 2020b).

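### EG/PCG allocation is called both stratified and matched-pairs, and the stated analysis uses neither strata nor pairs, which can only cost precision

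*Protocol article*

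**What the plan says.** Protocol article, section 2.3 (Assignment of interventions and blinding), on the two crossover groups:

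- "An external investigator will perform the randomization process (1:1"), so an external person randomises.
- The method is then named: "Stratified randomization will be carried out according to PD severity and general cognitive state".
- The sentence after that reads: "A matched-pairs design will be created in which participants were allocated to these two groups taking into consideration the outcomes". The variables meant are baseline values: Hoehn and Yahr stage (four levels) and MMP score in two classes (25 or more, 24 or less), both at T0.

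Section 2.1 places allocation after the T0 assessment.

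Section 2.4 (Data collection, management, and statistical analysis) fixes the main analysis as a two-factor mixed MANOVA "to analyze the effects of within-subject factors (assessment times) and the between-subject factor (group) on the outcomes registered". Carryover is examined by summing each participant's values over the two periods and comparing EG with PCG by a test for independent samples. Neither analysis has a term for stage, MMP class or pair.

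**The concern.** Stratified randomisation and pair matching have different units. Under stratification the participant is randomised within a cell, and the matching analysis carries the cell factors. Under pair matching the pair is randomised, and the matching analysis carries the pair. The article uses both labels for the same step and does not say how or when pairs are formed, or what happens to a participant without a match.

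Under either rule, allocation is balanced on stage and cognition by design. An analysis that omits these factors leaves their variance in the error term, although the design has already removed it from the EG versus PCG difference. The article itself gives grounds to expect them to matter: the introduction links fall risk to disease progression, and the discussion cites a relation between balance and cognition. At stake are precision in the randomised comparison and the ability of the carryover test to detect carryover.

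**Working it through.** **Plan's own figure.** The article gives no figure for within-pair or within-stratum correlation, so there is none to reproduce. The sample size enters only through the number randomised.

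**Inputs.**
- Cells: 4 stages × 2 MMP classes = 8 (section 2.3).
- Randomised share: two-thirds (abstract). 93 × 2/3 = 62, or 31 pairs; 112 × 2/3 = 74.7, about 75.
- Share of outcome variance explained by the allocation factors, R²: not given. Assumed 10%, 20% and 30%.

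**Step 1: one visit, or the sum over periods, unadjusted.** With balanced allocation and n per arm, the true variance of the EG–PCG difference is 2σ²(1 − R²)/n, while the unadjusted analysis estimates about 2σ²/n. The reported standard error is too wide by 1/√(1 − R²), and the true two-sided error is 2[1 − Φ(1.96/√(1 − R²))].

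| Assumed R² | SE ratio | True error at nominal 5% |
|---|---|---|
| 0.10 | 1/√0.90 = 1.05 | 3.9% |
| 0.20 | 1/√0.80 = 1.12 | 2.8% |
| 0.30 | 1/√0.70 = 1.20 | 1.9% |

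**Step 2: check by simulation.** 31 true pairs, 40,000 runs, unpaired against paired t-test; power at an illustrative standardised difference of 0.6.

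| Within-pair correlation | Unpaired error | Paired error | Unpaired power | Paired power |
|---|---|---|---|---|
| 0 | 5.1% | 5.1% | 0.64 | 0.63 |
| 0.1 | 3.9% | 4.9% | 0.65 | 0.68 |
| 0.2 | 3.0% | 5.0% | 0.66 | 0.72 |
| 0.3 | 2.0% | 5.1% | 0.67 | 0.78 |

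Both routes agree on direction and size. With no correlation, nothing is lost.

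**Step 3: what carries over to the planned analyses.** Write a participant's value at a visit as c + e, where c is the effect of stage and MMP class.
- Change: (c + e₁) − (c + e₀) = e₁ − e₀. An effect constant over time cancels, and the standard error of the group-by-time contrast is not inflated. Inflation remains only as far as stage or cognition predicts change, and the article gives no figure for that.
- Sum over two periods: (c + e₁) + (c + e₂) = 2c + e₁ + e₂. The effect stays, so Step 1 applies to the carryover comparison, with R² read as the share for the sum.

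**Step 4: predictability, as a secondary point.** If pairs are filled one after the other within the 8 cells, the second member's arm follows from the first's. With assumed uneven cell shares, about 47% of allocations (range 44% to 50%) are then determined for 62 to 75 randomised. If both members are in hand before the pair is randomised, the figure is 0%.

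**The case against.** **The two sentences may describe one design.** A matched pair inside a stage-by-MMP cell is a block of two, which is a form of stratified randomisation. This is a fair reading and makes the conflict one of unclear wording. The omission remains: on that reading the pair is the unit, and the stated analysis still ignores it.

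**The main contrast may lose little.** Step 3 bears this out. The 5% to 20% range must not be read as the loss in the group-by-time test.

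**Three stronger readings are tempting, and the article supports none of them.**

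- *Half the allocations can be foreseen.* Recruitment is consecutive ("The sampling process will consist in the consecutive non-probabilistic method"), and the principal investigators both confirm candidates ("the principal investigators called potential candidates to resolve possible doubts and confirm their participation") and handle "appointments after being assigned by telephone", so they know past assignments. But the article does not say that pairs are filled sequentially, and an external person randomises. The confirming call precedes the eligibility check and consent, and the values defining the cell are those at T0. Details of concealment are commonly left to the full protocol.
- *Unblinding one member of a pair unblinds the other.* Section 2.2.3 names two blinded assessors, a physiotherapist and a neuropsychologist. It does not say that either scores both factors or sees pair lists or entry order.
- *The mismatch produces false positives.* The error runs the other way.

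**Conclusion.** The point holds as one of clarity and precision. Section 2.3 leaves open whether strata or pairs generate the EG/PCG allocation, and section 2.4 names an analysis that reflects neither. The consequence is conservative: standard errors too wide, power lost, no rise in false positives. For the carryover test, the lost power means that carryover is more easily missed.

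The size rests on a correlation that the article does not give. For a single-visit or summed comparison it is about 5% to 20% on the standard error under an assumed 10% to 30% of variance explained, and nil if the factors explain nothing. For the group-by-time contrast it is probably smaller and not derivable. Comparisons with the ACG, which is neither randomised nor matched, are unaffected. Predictability is conditional: up to about half of allocations if pairs were filled in sequence and both the cell and past allocations were known, and none if pairs were complete before randomisation.

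**What to change.** 1. In section 2.3, state the single allocation rule actually used. If it was pairs, say when they were formed relative to randomisation and how unmatched participants were handled.
2. In section 2.4, add Hoehn and Yahr stage and MMP class, as used for allocation, as factors in the EG versus PCG model and in the carryover comparison. If stage or cognition is expected to affect change, let them interact with time. If pairs were the unit, use the pair instead.
3. Name in advance how sparse cells will be merged.

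**Cost.** A few sentences and some degrees of freedom. With 62 analysed, a two-group comparison has 62 − 2 = 60 error degrees of freedom. Main effects of stage (3) and MMP class (1) leave 56, all 8 cells (7) leave 53, and a paired analysis of 31 pairs leaves 30. At zero correlation, pairing lowered power only from 0.64 to 0.63.

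Pairs have a further cost. At the article's 20% dropout, assumed independent within pairs, 0.8 × 0.8 = 64% of pairs stay complete, so the pair is better fitted as a random effect that keeps single members than by dropping broken pairs. Participants already allocated need no new scheme; the rule used for them has to be reported and analysed as such.
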